| Measurements and procedures:    | 
Interested individuals will be informed (written and personally) and given at least 24 hours of consideration time before being invited to baseline (BL) measurements.
 
Healthy participants will be invited for a single baseline measurement of all primary and secondary outcomes.
 
Patients with CNLBP will be invited to baseline measurements after which they may still decide whether or not they would like to take part in the RCT trial. After a second assessment (pre-intervention, T0), included patients will then be randomly allocated to either the experimental (EG) or the control group (CG). All participating patients will receive standard physiotherapy. CG will receive additional exercise therapy (LIT), the EG will receive additional SMT.
 
One or two days after (T1) and four weeks after (FU) the last treatment, the project leader (PL) or the technical assistant will record the post-intervention assessment of the primary and secondary outcomes.
 
Each assessment will consist of a postural control task (standing on a labile platform and stabilising anticipated anterior-posterior sway), a head-repositioning task, and two questionnaires. Total duration will be approximately one hour.
 |

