| Number of Participants with Rationale: | 20 to 30 patients with low back pain (min. 10 per arm) and 20 healthy controls for the normative data. Based on previous studies with similar endpoints, the selected amount of participants has shown to suffice for an explorative approach with a desired power of 80% and an alpha of 0.05. |
| Study Duration:                        | September 2014 to December 2015                                                                                                                                                                                                                                                                 |
| Study Schedule:                        | Begin recruiting: January 2015
Last assessment: December 2015                                                                                                                                                                                                                                |
| Investigator and project leader:       | [name]
[contact]
[contact]                                                                                                                                                                                   |
| Study Centre:                          | Reha Rheinfelden
[name]

[name]                                                                                                                                                                                                                                   |
| Statistical Considerations:            | Student T-Test will be applied for group comparison at Baseline for cross-sectional comparison of LBP group with healthy group.

Repeated measure ANOVA with post-hoc analysis will be applied to test therapy effects.

Effect size will be calculated with Guyatt's effect size.  |
| GCP Statement:                         | This study will be conducted in compliance with the protocol, the current version of the Declaration of Helsinki, the ICH-GCP or ISO EN 14155 (as far as applicable) as well as all national legal and regulatory requirements.                                                                 |

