### **3.6 Explanation for choice of comparator (or placebo)**

Low intensity endurance training (LIT) does not provide a specific treatment effect to the sensorimotor system but can improve the global perception of well-being. Although no cardiovascular response is expected at these low intensities, LIT can help to gradually increase the level of activity and participation and is therefore recommended as part of CNLBP treatments [4]. Moreover, LIT is easily standardised and monitored throughout the trial duration.

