## 9.2 Assessments of outcomes

### 9.2.1 Assessment of primary outcome

Whilst preparing the setup and software configuration, the subject will be given 10 minutes time to fill in the personal data sheet, including the VAS scales for pain, and the ODI questionnaire for functional status. The questionnaires will be filled in by the patients at every measurement event (BL, T0, T1, and T2).

Self-reported impairment in daily activities will be assessed using the German version of the Oswestry Disability Index (ODI-D), which shows a good reliability. The ODI has ten sections about daily activities (pain, body hygiene, lifting objects, walking, sitting, standing, sleeping, sexual behaviour, social life, and travelling). Each section can be rated from 0 (no pain during activity or pain getting worse) to 5 (I cannot do it myself). The total score is in percentage of the total 50 points, if each section was answered (45, if 9 sections were answered, and so on). The end score will be from 0% (minimal impairment) to 100% (bedridden). A change of 4 points is considered as clinically relevant [26].

Self-reported pain will be assessed using the German version of the Visual Analogue Scale (VAS). It shows a good reliability with a correlation of 0.937 between the first and the second assessment. The VAS is a 100mm line with two endpoints representing the extreme states "no pain" and "pain as bad as it could be". A minimum of 13 mm difference on the scale is considered as clinical relevant [26].

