## 11. STATISTICAL METHODS

### 11.1 Hypothesis

- |                            |                                                                                                                                                                                                                      |
|----------------------------|----------------------------------------------------------------------------------------------------------------------------------------------------------------------------------------------------------------------|
| 1° Null Hypothesis:        | Functional status and self-reported pain will reduce significantly in both groups, CG and EG, but no group interaction is expected.                                                                                  |
| 1° Alternative Hypothesis: | EG will show significantly more improvement in all primary and secondary outcomes as compared to CG.                                                                                                                 |
| 2° Null Hypothesis:        | Compared to healthy controls, patients with CNLBP will show no difference in postural control with optimal joint configuration variability when adjusting COM after destabilisation as compared to healthy controls. |
| 2° Alternative Hypothesis: | Patients with CNLBP will show different postural variability to adjust to destabilisation as compared to healthy controls.                                                                                           |
| 3° Null Hypothesis:        | Compared to healthy controls, patients with CNLBP will show no difference in cervical proprioception acuity as compared to healthy controls.                                                                         |
| 3° Alternative Hypothesis: | Patients with CNLBP will show reduced cervical proprioception acuity as compared to healthy controls.                                                                                                                |

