## **11.4 Planned Analyses**

Baseline imbalance between groups will be tested with a student t-test. Differences in means between healthy participants and patients with CNLBP will be analysed with independent student t-tests. A mixed (2) Group x (2) ME ANOVA with repeated measures during ME will be conducted for each dependent variable individually (Pain VAS, Functional Status ODI, Postural Control COM and CM, Proprioception JRE, and Motor Equivalence UCM).

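### The only effect size the protocol names, Guyatt's, does not in its usual form measure the EG-versus-CG contrast, and it can be sizeable in both arms when SMT adds nothing

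*Protocol*

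**What the plan says.** The synopsis (Statistical Considerations) says of the trial part: "Repeated measure ANOVA with post-hoc analysis will be applied to test therapy effects". The next paragraph is one sentence: "Effect size will be calculated with Guyatt's effect size". It gives no formula, denominator, group or time points. Section 11 does not mention an effect size, so this sentence is the whole of the plan on the matter.

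The hypothesis concerns a difference between arms. Section 11.1 gives the primary alternative as "EG will show significantly more improvement in all primary and secondary outcomes as compared to CG" and the primary null as "Functional status and self-reported pain will reduce significantly in both groups, CG and EG, but no group interaction is expected". Section 11.4 specifies the test: "A mixed (2) Group x (2) ME ANOVA with repeated measures during ME will be conducted for each dependent variable individually".

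On what each group receives, the synopsis states: "All participating patients will receive standard physiotherapy". CG has low-intensity endurance training (LIT) in addition, of which section 3.6 says: "LIT can help to gradually increase the level of activity and participation and is therefore recommended as part of CNLBP treatments". Healthy participants are measured once.

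**The concern.** Guyatt's index was designed to show how responsive an instrument is. Its usual numerator is the mean change in a treated group, and its usual denominator is the SD of change in people whose condition is stable. Neither part contains the difference between EG and CG. Change due to physiotherapy, natural course or regression to the mean enters the numerator in full.

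The trial calls itself a pilot (section 6.1) and explorative (section 11.2), with a minimum of 10 patients per arm. With 10 per arm, a two-sided t-test at 5% has 80% power only for a standardised difference of about 1.32. For a difference of 0.5 the power is about 19% (26% with 15 per arm). Unless the effect is very large, the interaction test may well be inconclusive, and readers would then look to the reported effect size. An index that is sizeable in EG could be taken as the effect of adding SMT when the same value would be found in CG.

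**Working it through.** **No plan figure to reproduce.** The protocol reports no value for Guyatt's index and gives no VAS or ODI standard deviation. The work below is for VAS, because section 9.2.1 gives a retest correlation for VAS but no such figure for ODI.

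**Inputs from the protocol.** Retest correlation: "It shows a good reliability with a correlation of 0.937 between the first and the second assessment" (section 9.2.1). Clinically relevant VAS difference: 13 mm (section 9.2.1). Patients per arm: 10 (section 11.2), with 20 to 30 patients in total (synopsis), so up to 15 per arm.

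**Assumptions.** VAS SD of 15 to 30 mm; a common improvement of 13 mm in both arms; a true between-arm difference of 0; the 0.937 correlation applied to the interval from BL to T0.

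**1. Which group could supply the denominator?**
- Healthy participants have one measurement and so no change score.
- CG is treated from T0 to T1 and is expected to improve, so it is not stable.
- BL to T0 is the only interval before treatment. It lasts a few days, and the text does not link it to the effect size.

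**2. What the primary null alone implies.** A significant reduction within an arm (paired t, two-sided 5%) requires mean change / SD of change ≥ t / √n.
- n = 10: 2.262 / √10 = 0.72
- n = 15: 2.145 / √15 = 0.55

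If both arms improve significantly and their change SDs are similar, a ratio with a change-SD denominator is already about 0.55 to 0.72 or more in each arm, with no added effect of SMT. This step needs no assumed VAS SD.

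**3. Denominator from BL to T0.** SD of stable change = SD × √(2 × (1 − 0.937)) = SD × 0.355. Index = 13 / SD of stable change.

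| Assumed VAS SD (mm) | SD of stable change (mm) | Index, EG and CG alike | Between-arm effect |
|---|---|---|---|
| 15 | 5.32 | 2.44 | 0 |
| 20 | 7.10 | 1.83 | 0 |
| 25 | 8.87 | 1.46 | 0 |
| 30 | 10.65 | 1.22 | 0 |

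**4. Sensitivity to the stable correlation (VAS SD 20 mm).**
- r = 0.7: SD of change = 20 × √0.6 = 15.5 mm, index = 13 / 15.5 = 0.84
- r = 0.5: SD of change = 20 × √1.0 = 20 mm, index = 13 / 20 = 0.65

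**5. Sampling variation.** The simulation used 20,000 trials per setting, 10 per arm, both arms improving by 13 mm, VAS SD 15 to 25 mm and an SD of individual response of 0 to 20 mm.
- BL-T0 denominator: median index about 1.5 to 2.5; above 0.8 in 81% to 100% of trials.
- CG change SD as denominator: median about 0.6 to 2.5; above 0.8 in 31% to 100%.
- Between-arm standardised difference: median about 0.
- t-test of change between arms, equivalent to the 2 x 2 interaction: rejects in about 5%.

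**The case against.** The strongest reply is that the protocol writes out no formula. The within-group form is the customary one, and a version with the between-arm difference in the numerator is not excluded. A formula can also be left to a statistical analysis plan. This stands in part. A reader might infer that the protocol has committed itself to a within-group effect size, but the text only names an index whose usual form is within-group. Any between-arm variant would still need defining, and the same edit does that.

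The sentence is also a paragraph of its own, tied neither to the t-test nor to the ANOVA. A responsiveness index could suit the proposed postural measure or the retest analysis planned in section 13. That is possible, but the sentence directly follows the one on testing therapy effects and no other effect size is offered, so a reader will take it as the therapy effect size.

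A reader might further infer that the primary analysis misses the randomised contrast. It does not: the Group x ME interaction tests it and keeps its 5% error rate. A misleading claim for SMT would need the EG index reported without the CG index or the interaction, and the protocol does not say that this will happen.

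Finally, a reader might infer that the index is bound to look large. The documents do not support this either. The 0.937 is a general reliability figure, with nothing to show that it holds from BL to T0 in these patients. The 13 mm is a relevance threshold, not an expected improvement. Lower stable correlations, or a CG change SD with variable response, bring the index down to about 0.6 to 0.8. These limits stand, and the conclusion is worded accordingly.

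**Conclusion.** The concern holds for the reported effect size only. The one measure named does not, in its usual form, estimate the EG-versus-CG contrast, and no group is untreated and stable over T0 to T1 to supply its denominator. Under the protocol's own null the index can be moderate to very large in both arms while the between-arm effect is 0. It is about 0.55 to 0.72 or more with a change-SD denominator, given similar change SDs in the two arms. The range of 1.2 to 2.4 rests on a BL-T0 SD that follows the 0.937 correlation, a 13 mm change in both arms and a VAS SD of 15 to 30 mm. The first range follows from significance in each arm; the second is illustrative and shrinks as the stable correlation falls. The point should be corrected, but it does not put the primary test at risk.

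**What to change.** In the synopsis and section 11.4, replace the effect-size sentence with wording such as: *The therapy effect size is the EG-minus-CG difference in change from T0, in mm VAS and in ODI points, with 95% CI. A standardised between-arm version, with its standardiser named (for example the pooled T0 SD), is reported alongside it, also with 95% CI.* The choice of standardiser is open, provided it is fixed in advance.

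If Guyatt's index is kept, define its numerator and denominator (for instance the SD of change from BL to T0), limit it to instrument responsiveness, for example in the retest analysis, and state that it is not the treatment effect.

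The cost is one sentence in each of two places, with no new data and no change to the primary test. The effect size reported for SMT may be smaller than a within-group index would show.

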## **STUDY SUMMARY IN LOCAL LANGUAGE**

### **Effekte eines sensomotorischen Trainings auf posturale Kontrolle und Schmerz: Eine einfachblinde, parallel randomisierte Studie**

Chronischer Rückenschmerz ist nach wie vor die häufigste Ursache verminderter Lebensqualität und steigenden Arbeitsausfällen, was mit hohen sozioökonomischen Kosten verbunden ist. Sensomotorisches Training wird dabei sehr häufig in der Schmerzrehabilitation eingesetzt, da angenommen wird, dass das Schmerzempfinden mit der Körperwahrnehmung und Haltungskontrolle zusammenhängen. Eine Verbesserung der Körperwahrnehmung durch Sensomotorisches Training soll so zur Reduktion der Schmerzen und auch zur verbesserten Haltungskontrolle führen. Bisher wurden aber noch keine Studien durchgeführt, welche die Effektivität dieser Trainingsmethode untersuchten.

Diese Studie verfolgt zwei Ziele. Einerseits sollen die Haltungskontrolle und die Körperwahrnehmung zwischen Gesunden und Patienten mit chronischen Rückenschmerzen verglichen werden. Zur Messung der Haltungskontrolle wird ein Parameter vorgestellt, der es ermöglichen soll, die zeitabhängige Veränderung der Haltung zu erfassen. Bisherige Messmethoden erlauben nur eine statische Analyse der Haltung, die wenig Aussagen zur funktionellen Haltungskontrolle erlauben. Um die Körperwahrnehmung zu vergleichen, wird die Fähigkeit untersucht, eine vorgegebene Kopfposition mit geschlossenen Augen einzunehmen.

Als zweites Ziel soll die Wirksamkeit einer sensomotorischen Trainingsmethode auf labiler Unterlage untersucht werden (posturale propriozeptive Therapie). Patienten, die nach der beschriebenen Erstuntersuchung an der Interventionsstudie teilnehmen möchten, werden zufällig in eine von zwei Trainingsgruppen eingeteilt. Beide Gruppen erhalten neun Einheiten konventioneller Physiotherapie die jeweils 30 Minuten dauern. In der Experimentalgruppe wird zusätzlich ein 15-minütiges sensomotorisches Training angeboten. Die Kontrollgruppe erhält niederschwelliges Ausdauertraining derselben Dauer. Um allfällige Veränderungen zu messen, werden Parameter der Haltungskontrolle und das persönliche Schmerzempfinden sowie Einschränkungen im Alltag der Patienten erfasst. Für die Studie werden insgesamt vier Messungen stattfinden: Erstuntersuchung beim Vergleich mit gesunden, Zweituntersuchung zum Ermitteln der Ausgangswerte unmittelbar vor der ersten Therapie, Nachfolgeuntersuchung unmittelbar nach der letzten Therapie sowie eine weitere Nachkontrolle vier Wochen nach der Intervention.

## ABBREVIATIONS

Provide a list of abbreviations used on the protocol - to be completed

|       |                                                |
|-------|------------------------------------------------|
| AE    | Adverse Event                                  |
| BL    | Baseline                                       |
| BOS   | Base of support                                |
| CEC   | Competent Ethics Committee                     |
| CG    | Control group                                  |
| CNLBP | Chronic non-specific low back pain             |
| COM   | Centre of mass                                 |
| COP   | Centre of pressure                             |
| CRF   | Case Report Form                               |
| DSMC  | Data Safety Monitoring Committee               |
| EG    | Experimental group                             |
| EKNZ  | Ethikkommission Nordwest-und Zentralschweiz    |
| GCP   | Good Clinical Practice                         |
| H0    | Null hypothesis                                |
| H1    | Alternative hypothesis                         |
| HFG   | Humanforschungsgesetz (Law on human research)  |
| IIT   | Investigator-initiated Trial                   |
| IMP   | Investigational Medicinal Product              |
| ISO   | International Organisation for Standardisation |
| ITT   | Intention to treat                             |
| LBP   | Low back pain                                  |
| LIT   | Low-intensity endurance training               |
| MD    | Medical Device                                 |
| ODI   | Oswestry Disability Index                      |
| PL    | Principal Investigator                         |
| PL    | Project Leader                                 |
| PPT   | Postural proprioceptive training               |
| SDV   | Source Data Verification                       |
| SMT   | Sensorimotor training                          |
| SOP   | Standard Operating Procedure                   |
| SPC   | Summary of product characteristics             |
| SUSAR | Suspected Unexpected Serious Adverse Reaction  |
| T0    | Assessment before intervention                 |
| T1    | Assessment directly after intervention         |
| T2    | Assessment 4 weeks after end of intervention   |
| TMF   | Trial Master File                              |
| UCM   | Uncontrolled Manifold                          |
| VAS   | Visual Analogue Scale                          |

## STUDY SCHEDULE

**Table 1: Study procedure**

| Study events               | Recruiting    | Baseline(BL)  | Pre-intervention (T0) | Intervention                     | Post-intervention (T1) | Follow-up (T2) |
|-----------------------------------|----------------------|----------------------|------------------------------|-----------------------------------------|-------------------------------|-----------------------|
| Visit                             | 0 (phone)            | 1                    | 2                            | 3-12                                    | 13                            | 14                    |
| Duration                          | 1x20'                | 1x60'                | 1x60'                        | 9x45'                                   | 1x60'                         | 1x60'                 |
| Time                              | 1 st week | 1 st week | 1 st week         | 1 st to 5 th week | 5 th week          | 9 th week  |
| Patient information               | x                    |                      |                              |                                         |                               |                       |
| Written consent                   |                      | x                    |                              |                                         |                               |                       |
| Socio-demographic characteristics |                      | x                    |                              |                                         |                               |                       |
| Medical history                   | x                    |                      |                              |                                         |                               |                       |
| Eligibility                       | x                    | x                    |                              |                                         |                               |                       |
| Randomisation                     |                      |                      |                              | x                                       |                               |                       |
| Therapies                         |                      |                      |                              | x                                       |                               |                       |
| Primary outcomes                  |                      | x                    | x                            |                                         | x                             | x                     |
| Secondary outcomes                |                      | x                    | x                            |                                         | x                             | x                     |
| Documentation of adverse events   |                      |                      | x                            | x                                       | x                             | x                     |

